## Abstract

**Background:**

East and Southern Africa have the highest HIV incidence and prevalence in the world, with adolescents and young adults being at the greatest risk. Despite effective combination prevention tools, including the recently available pre-exposure prophylaxis (PrEP), HIV incidence among adolescents and young adults in Uganda remains high, and PrEP use remains low. Mental health and substance use (behavioral health) play a role in sexual behavior and decision-making, contributing to an increase in the risk for acquiring HIV. Interventions that target multiple HIV risk factors, including sexual and mental health and problematic substance use, are crucial to ending the HIV epidemic. Yet few interventions addressing HIV related health disparities and comorbidities among adolescents and young adults in East and Southern Africa currently exist.

**Objective:**

This study aims to evaluate the acceptability and feasibility of Kirabo, an SMS text message intervention informed by the information, motivation, and behavior model and to be disseminated through secondary schools. The study will gather preliminary estimates of Kirabo’s effectiveness in increasing HIV testing and linking users to mental health counselors.

**Methods:**

We identified Mobile 4 Reproductive Health for adaptation using the assessment, decision, administration, production, topical experts, integration, training, testing (ADAPT-ITT) framework. Mobile 4 Reproductive Health is an evidence-based automated 2-way SMS text messaging and interactive voice response platform that offers sexual and reproductive health information and links users to HIV clinics in East Africa. Through ADAPT-ITT we refined our approach and created Kirabo, an SMS text message–based intervention for linking adolescents and young adults to health services, including HIV testing and mental health counseling. We will conduct a 2-arm randomized controlled trial in Masaka, Uganda. Adolescents (N=200) will be recruited from local schools. Baseline sociodemographic characteristics, HIV test history, and behavioral health symptoms will be assessed. We will evaluate acceptability and feasibility using surveys, interviews, and mobile phone data. The preliminary efficacy of Kirabo in increasing HIV testing and linking users to mental health counselors will be evaluated immediately after the intervention and at the 3-month follow-up. We will also assess the intervention’s impact on self-efficacy in testing for HIV, adopting PrEP, and contacting a mental health counselor.

**Results:**

Intervention adaptation began in 2019. A pretest was conducted in 2021. The randomized controlled trial, including usability and feasibility assessments and effectiveness measurements, commenced in August 2023.

**Conclusions:**

Kirabo is a tool that assists in the efforts to end the HIV epidemic by targeting the health disparities and comorbidities among adolescents in Uganda. The intervention includes local HIV clinic information, PrEP information, and behavioral health screening, with referrals as needed. Increasing access to prevention strategies and mitigating factors that make adolescents and young adults susceptible to HIV acquisition can contribute to global efforts to end the HIV epidemic.

**Trial Registration:**

ClinicalTrials.gov NCT05130151; https://clinicaltrials.gov/study/NCT05130151

**International Registered Report Identifier (IRRID):**

DERR1-10.2196/49352

## Introduction

### Background

Globally, adolescents and young adults aged 10 to 24 years represent approximately 30% of people living with HIV. East and Southern Africa (ESA) have the highest HIV incidence in the world, with adolescents and young adults being at the greatest risk [1-3]. AIDS is the leading cause of death for adolescents and young adults in the region and the second leading cause of death for adolescents and young adults worldwide [4,5]. Despite combination prevention efforts, including pre-exposure prophylaxis (PrEP) [6], HIV incidence among adolescents and young adults remains high [1], and PrEP use remains low [7]. Further, in part owing to the lack of access to information and services related to mobility, the uptake of antiretroviral therapy among adolescents and young adults in Uganda living with HIV is considerably lower than that among adults in Uganda living with HIV [8-10].

Mental health and substance use affect decisions regarding sexual and reproductive health (SRH) and can increase the risk for acquiring HIV infection [11-13]. It is estimated that mental illness contributes to an estimated 4- to 10-fold increase in the risk for acquiring HIV [14-17]. In Uganda, alcohol is the primary substance used, and the country has one of the highest per capita alcohol consumption rates in ESA [18,19]. Thus, in the proposed protocol, we primarily focus on alcohol consumption. It is widely recognized that designing interventions for addressing multiple HIV risk factors, including sexual and mental health and problematic substance use, is crucial to ending the HIV epidemic, yet few such interventions currently exist for adolescents and young adults in ESA [20]. Integrating screening for mental health and alcohol use problems with appropriate referral mechanisms into existing SRH interventions may be a feasible first step toward addressing this gap.

In Uganda, household mobile phone ownership has risen dramatically over the last 15 years, from approximately 10% in 2004 to 74% in 2020, yet few people own smartphones [21,22], with a similar pattern in the specific region of study [23,24]. SMS text messages can be sent or received using any mobile phone, and SMS text messaging is the most widespread means of communication in ESA [25,26]. Systematic reviews have indicated that SMS text messaging is a feasible and acceptable method for delivering health interventions [27] focused on substance use [28], mental health [29], and HIV prevention and care [30,31]. Mobile phone–based HIV interventions in ESA are well represented in the literature. However, most mobile phone–based interventions that focus on mental health and substance use have been implemented in Europe and the United States [27-29].

### This Study

This study focuses on adolescents aged 15 to 19 years who are in secondary school in the greater Masaka region of Uganda. This is a critical developmental time for intervention, as many adolescents within this age range begin to leave school, search for work, and engage in sex and are thus at an increased risk for HIV infection [32-36]. This is also the age when, if at risk, symptoms of mental disorders typically emerge [37-40]. Consequently, this stage of adolescence is a critical time for preventive interventions, and our preliminary qualitative work shows the importance of mobile phones for finding sexual partners and the as-yet-underused potential for mobile phones to promote health [23]. As noted earlier, mental health and alcohol abuse are associated with an increased risk for HIV infection. Thus, screening adolescents with mental health or alcohol use problems and linking them to counselors may help address these factors and reduce the risk for HIV infection. We identified the local mental health partner StrongMinds (authors CO, CT, CN, and VM). StrongMinds is an international nongovernmental organization in Uganda that offers free evidence-based, telehealth-based group interpersonal therapy [41-47].

Through our formative work described in the subsequent section, we used the ADAPT-ITT (assessment, decision, administration, production, topical experts, integration, training, testing) [48] framework to adapt and update a mobile phone–based SRH intervention. Our adapted intervention, named Kirabo, is also informed by the information, motivation, and behavior (IMB) model [49] and uses automated SMS text messaging to link adolescents to HIV testing and mental health counselors. Through the proposed research, we will evaluate the feasibility and acceptability of Kirabo and generate the preliminary estimates of Kirabo’s efficacy in HIV testing. Adolescents today rely heavily on mobile phones for information and services; therefore, we believe that the proposed intervention could be applied and adapted across ESA and potentially in other underresourced settings [21,50,51].

## Methods

### Formative Work

We used the ADAPT-ITT [48] framework (Table 1) to adapt an existing evidence-based SRH mobile phone intervention, Mobile 4 Reproductive Health (m4RH), originally designed by FHI 360 [52-55]. Through our formative work, including discussions with our in-country research team (RK, OIN, and PN), we named our adapted intervention *Kirabo*, a Luganda-language gender neutral name that means “gift.” In the subsequent section, a detailed description of the adaptation process is provided, including our summary of prior findings and context, a description of the Kirabo pretest, and the proposed design of our randomized controlled trial (RCT) pilot study. Researchers at the HIV Center for Clinical and Behavioral Studies at the New York State Psychiatric Institute (NYSPI) and Columbia University (CU), in collaboration with researchers at the Ugandan office of the International Center for Child Health and Development (ICHAD) at the University of Washington in St Louis, conducted this formative work. Study participants were recruited from secondary schools in southwest Uganda, one of the regions hardest hit by HIV [1]. This region is bordered by Lake Victoria. Most of the population (80%) lives in rural communities and engages in small-scale agriculture. Most of the population (75%) is aged under 30 years [56], and the Ugandan government policy supports HIV testing and PrEP for adolescents, whom they have designated a *priority population* [6]. In the region of study, HIV clinics provide free HIV testing, PrEP, and antiretroviral treatment, although the uptake of these services among adolescents and young adults is persistently low and HIV incidence has remained high [1,6,7,57].

**Table 1 table1:** ADAPT-ITT^a^ phases.

Phase	Methodology
1. Assessment (formative)	Analyses of quantitative and qualitative secondary data
2. Decision	Publish formative findings Submit IRB^b^ protocol
3. Administration	Administer pretest in Uganda (24 adolescents and young adults)
4. Production	Produce mobile phone–based EBI^c^ draft 1
5. Topical experts	Identify and review “product” with experts
6. Integration	Integrate expert input to create pilot-ready EBI
7. Training	Train staff to implement EBI draft 2
8. Testing and evaluation	Pilot study Initiate evaluation Mixed methods: interviews, pre-post surveys, and mobile phone data

^a^ADAPT-ITT: assessment, decision, administration, production, topical experts, integration, training, testing.

^b^IRB: institutional review board.

^c^EBI: evidence-based intervention.

### Phases 1 and 2: Assessment and Decision

#### Overview

We first conducted formative work that involved secondary data analysis of both quantitative and qualitative data to assess how mobile phones may be associated with health risks and may also present opportunities for intervention [23,58,59]. Through our longitudinal analyses among youths in southern Uganda, we found that for adolescents and young adults, mobile phone ownership was associated with social and health behaviors; adolescents and young adults who owned phones were more likely to have multiple and concurrent sexual partners, and adolescent and young adult men who owned phones were more likely to be circumcised [23,24,34,58]. Furthermore, our mixed methods analysis demonstrated how mobile phones were a key tool that adolescents and young adults used to make social and economic connections. In qualitative interviews, adolescents and young adults also expressed an unmet need for mobile phones to provide health information [23]. Adolescents and young adults in southern Uganda are highly mobile, as structural factors, such as the lack of available employment, force adolescents and young adults to move after they leave school and search for work [34]. Mobility makes it difficult to track adolescents and young adults for recommended health care services [8], and mobility is also associated with a greater risk of HIV infection [32-34]. Thus, mobile phones present an opportunity to reach adolescents and young adults with high mobility [25,26,34,50]. We identified m4RH as a candidate for adaptation. m4RH is an evidence-based [52-55] automated 2-way SMS text messaging and interactive voice response (IVR) platform that offers SRH information and links users to HIV clinics in East Africa [52-55]. IVR is an automated technology that allows incoming callers to access information via a voice response system of prerecorded messages. Communicating via the platform is free in Uganda and across East Africa owing to existing agreements between FHI 360, which designed the original m4RH platform, and the regional mobile phone service provider Airtel. However, m4RH was not specifically tailored to adolescents, and it did not include PrEP information, nor did it include any behavioral health elements.

#### The IMB Model

The IMB model [49] guided our design of new content for the adapted intervention. The IMB model posits that information (in this project, communicated through interactive SMS text messages), motivational factors, and behavioral skills (measured through self-efficacy and intentions) influence the adoption of a new behavior (HIV testing, PrEP uptake, and mental health counseling). Our adapted SMS text messages, beyond communicating basic facts, were organized through narratives, which appealed to emotions, imagination, and value systems [60-63]. Narrative components influence how people think, behave, and develop lasting health-related behaviors and, therefore, influence both information and motivational factors. In the IMB model, *motivational factors* include *positive outcome expectancies*, for example, starting PrEP will enable me to achieve future goals by protecting me from getting HIV; *negative outcome expectancies* are undesirable consequences (eg, HIV infection). Motivational factors that may be enhanced by engaging with the mobile phone platform include *perceived risk*; perceptions of *peer norms*, that is, whether a new behavior is perceived positively or negatively by important referents, such as partners, other women, or family; and *barriers to and facilitators* of adopting preventive behaviors*.* The IMB model also highlights the importance of increasing *behavioral skills* and a sense of self-efficacy in adopting prevention practices and persisting despite barriers. In short, self-efficacy is a person’s confidence in their ability and skills to perform a behavior [64]. We posit that SMS text messaging via the platform will increase adolescents’ self-efficacy by providing them with simple and direct information (including information about HIV prevention skills, clinic location and contact numbers, and information about behavioral health counselors), thus promoting their belief that they can perform the target behavior successfully (eg, going to the clinic and taking an HIV test).

#### Three Main Modifications

In Kirabo, we made the following three main modifications to the existing m4RH approach:

In prior work, m4RH was disseminated via radio and magazine advertisements and at family planning clinics [52,53,55,65]. To ensure that we reach the target population of adolescents for Kirabo, we partnered with local schools and will disseminate Kirabo at the schools or via SMS text messages. Our researchers will deliver an IMB-informed oral script, describing Kirabo in person at local schools and further disseminating Kirabo via flyers.When m4RH was designed, PrEP was not available in sub-Saharan Africa. Thus, in Kirabo, we added and updated the existing m4RH HIV prevention menu to include the current information on PrEP and the location of local clinics. To create PrEP messages, we used text from the Centers for Disease Control and Prevention’s (CDC) informational materials and published qualitative research studies [66-68]. Figure 1 displays an example of PrEP messages from Kirabo, with the numbers indicating user responses and menu selections. In Figure 1, Kirabo asks the adolescent the following question: “have you heard of PrEP? Reply 1 for Yes, 2 for No.” The adolescent then replies “2,” indicating that they had not previously heard of PrEP and thus triggering Kirabo to begin to describe PrEP. Furthermore, we added additional details, such as local landmarks, directions, and contact numbers for local HIV clinics. As part of this formative work, we contacted 6 HIV clinics in the southern Ugandan region. Of the 6 clinics, 5 confirmed that they were currently able to prescribe PrEP to adolescents according to the national guidelines and had ample PrEP medication in supply [69]. The clinic location and contact information were included in the adapted intervention.Finally, because we know that mental health is critical to HIV prevention efforts, in Kirabo, we additionally focus on behavioral health. Adolescents will complete screeners, which are then used to tailor the SMS text messages they receive.

**Figure 1 figure1:**
[figure not shown]
Pre-exposure prophylaxis (PrEP) messages.

For mental health, we will measure depression using the 4-item Patient Health Questionnaire (PHQ-4), which includes the first 2 questions of the 9-item Patient Health Questionnaire (PHQ-9) [70] and the first 2 questions of the 7-item Generalized Anxiety Disorder Questionnaire (GAD)-7 for assessing anxiety [71]. For example, question 1 of the PHQ reads, “over the last two weeks, how often have you had little interest or pleasure in doing things?” Possible responses range from “not at all (0)” to “nearly every day (3).” Individuals who score ≥1 on the first 2 questions of the PHQ-9 or GAD-7 will be directed to complete the full measure. If the respondents score 0 on the first 2 questions of these measures, the system will respond with a brief message thanking them for their time. To be cautious and consistent with StrongMinds’ approach, we will use a cutoff point of 8 on the PHQ-9 to determine a referral to a StrongMinds counselor. Additional information regarding these measures is provided in Table 2.

**Table 2 table2:** Additional information regarding measures and their times of collection.

Construct		Measures	Time
**Behavioral, mental health, and alcohol use measures**			
	Demographics	Items developed for previous Suubi studies [72-74], including age, sex, parents’ occupation, household size, orphanhood status, primary caregiver, and community of origin	Baseline
	COVID-19 experiences	CASPE^a^ (adapted from Suubi+Adherence [74] and the study by Ladouceur [75])	Baseline
	HIV testing	Self-report of HIV test (yes/no; past year [at baseline], during the study period [immediately after the intervention], and past 3 months [at follow-up]) confirmed with proof of results from the clinic using measures and procedures adapted from Suubi studies [72-74]	Baseline, immediately after the intervention, and 3-month follow-up
	Intention to test for HIV	Questions adapted from a study of secondary school students in Uganda [76]	Baseline, immediately after the intervention, and 3-month follow-up
	Self-efficacy	Questions adapted from a study with secondary school students in Uganda [76] and a study with high school students in the United States [77], including questions regarding self-efficacy in testing for HIV, trying PrEP^b^, using condoms consistently, contacting a behavioral health counselor	Baseline, immediately after the intervention, and 3-month follow-up
	Current HIV prevention strategies	This measure includes items developed for previous Suubi studies [72,73] in Uganda (in addition to a question regarding PrEP; range 5-25; 5 question items; α=.70), for example, “I think it is very important to use condoms every time one has sex,” “as a teenager I think AIDS is a threat to my health,” and “I think all people my age who have sex should use condoms.” Scores range from 4: strongly agree; 3: somewhat agree; 2: somewhat disagree; to 1: strongly disagree.	Baseline, immediately after the intervention, and 3-month follow-up
	HIV-related knowledge	This measure includes items from previous Suubi studies [72,73] in Uganda; this measure includes 13 items about HIV infection and prevention mechanisms (range 0-16; 16 question items; α=.83), for example, “HIV can be passed by an infected person even though that person is not feeling sick.” Possible scores are 1: true; 2: false; and 3: don't know or 1: not sure; 2: unsafe; and 3: safe.	Baseline, immediately after the intervention, and 3-month follow-up
	Sexual risk behaviors	This measure includes items from previous Suubi studies [72,73] in Uganda (range: 5-25; 5 question items; α=.76), for example, “I believe it’s OK to have sex without protection with someone you know.” Scores range from 1: never; 2: sometimes; 3: about half of the time; 4: most of the time; to 5: always.	Baseline, immediately after the intervention, and 3-month follow-up
	PrEP knowledge	Adapted 13-item true-false questionnaire on PrEP knowledge [78,79] including questions such as “PrEP is a pill you can take to prevent HIV” and “PrEP is only for people who are HIV negative”	Baseline, immediately after the intervention, and 3-month follow-up
	Depressive symptomatology	PHQ-9^c^ [70], a standardized 9-item self-report instrument used to assess depression, is used. Participants rate the frequency of their symptoms over the past 2 weeks. Items are rated on a 4-point scale, ranging from 0 (not at all) to 3 (nearly every day), and scale scores range from 0 to 27. PHQ-9 scores of 5 to 9 represent minimal to mild depression and 10 to 20 represent moderate to severe depression. A score ≥10 has a sensitivity of 88% and a specificity of 88% for major depression.	Baseline and immediately after the intervention
	Anxiety	GAD-7^d^ [71], is a standardized instrument that asks participants to rate their symptoms over the past 2 weeks on a 4-point scale ranging from 0 (not at all) to 3 (nearly every day), is used. Overall scores for the GAD-7 range from 0 to 21. At a cutoff point of 10 (indicative of clinically significant symptoms), the sensitivity and specificity of the scale equal 89% and 82%, respectively. The GAD-7 has a Cronbach α of.92, indicating good internal consistency, and an intraclass correlation of 0.83, indicating good procedural validity.	Baseline and immediately after the intervention
	Alcohol use disorder screen	AUDIT-C^e^ [80,81], a 3-item screener excerpted from the full standardized 10-item AUDIT tool for assessing hazardous alcohol consumption, is used. Items are scored on a 5-point scale for a possible score of 0 to 12. The higher the score, the higher the risk of hazardous alcohol consumption. AUDIT-C scores of ≥4 in men and ≥3 in women are considered positive for hazardous alcohol consumption.	Baseline and immediately after the intervention
	Reported (and confirmed) sessions with mental health counselor	Self-report and local school and clinic records	Baseline and immediately after the intervention
	Peer messaging	Self-report of messages shared with peers	Baseline and immediately after the intervention

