Most adolescents preferred SMS text messaging. Thus, to streamline our delivery, recruitment, and evaluation, we decided to focus on SMS text messaging in this pilot RCT. In addition, to protect privacy, we added an initial message to be sent on each day of the intervention period that asked, “is this a good time to chat?” By contrast, the initial prompt from the pilot test immediately introduced the topic of the day (HIV testing, mood, etc). If adolescents respond with “yes,” then they would be sent the follow-up message that introduces the topic of the week. If adolescents respond with “no,” they would be sent a message that says, “ok thanks, write back with yes when you are free and available.”In the pretest, adolescents who screened positive for symptoms of depression, anxiety, or hazardous alcohol were provided with the contact number of the general StrongMinds counselor. As described earlier, adolescents expressed concern that they would incur charges by calling StrongMinds counselors. Therefore, we revised our methods (including language in our consent forms), and in the RCT, we will provide a daily update to StrongMinds counselors with a list of contact numbers of adolescents who screened positive for symptoms of depression, anxiety, or hazardous alcohol use.On the basis of our initial focus group discussions and our presentation at the HIV Implementation Science Fellowship, we expect that a 3-month follow-up will be sufficient to determine feasibility and accessibility. In addition, a shorter follow-up period will limit the possibility of unforeseen historical or COVID-19–related interruptions.

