### Phases 7 to 8: Training and RCT Pilot Study

#### Procedures

We plan to conduct a 2-arm, randomized controlled study via mobile phones among adolescents in the greater Masaka region of Uganda. We will compare Kirabo to an inactive control and evaluate whether adolescents who interacted with Kirabo had higher rates of self-reported HIV testing (yes/no; verified with the HIV clinic when possible) immediately after the intervention and at the 3-month follow-up assessment. Secondary outcomes include differences in condom use, PrEP knowledge, PrEP uptake for eligible patients, HIV-related knowledge and sexual risk behaviors, and antiretroviral treatment uptake for eligible patients. Exploratory aims include the number of participants who screen positive for symptoms of depression, anxiety, and hazardous alcohol use and the proportion of confirmed linkages to mental health counseling.

Adolescents (aged 15-19 years) in the greater Masaka region in southern Uganda who own a mobile phone will be eligible for the trial. Adolescents will be involved in the trial for approximately 5 weeks with a 3-month follow-up assessment (Figure 2). After informed assent and parental permission, the baseline assessment, and confirmation of eligibility, adolescents will be randomly assigned to the Kirabo intervention group or standard of care group. Randomization will be performed in a 1:1 ratio and stratified by gender and school (to minimize contamination) with a block size of 10. We anticipate recruiting students from 20 schools. The treatment assignments will be generated using a pseudorandom number generator. An electronic list of IDs, access codes, and credentials will be provided securely to the sites.

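### Linkage to a mental health counselor is to be evaluated at 3 months, but Table 2 schedules no counselor-session collection at that visit

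*Protocol article*

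**What the plan says.** The Methods paragraph of the abstract pairs two efficacy targets, HIV testing and linkage, and times them together: "linking users to mental health counselors will be evaluated immediately after the intervention and at the 3-month follow-up".

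Table 2 gives each measure with its collection times. The row for linkage is "Reported (and confirmed) sessions with mental health counselor", its source is "Self-report and local school and clinic records", and its time is "Baseline and immediately after the intervention". Other rows, including HIV testing and self-efficacy, read "Baseline, immediately after the intervention, and 3-month follow-up".

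The Procedures section lists "the proportion of confirmed linkages to mental health counseling" among the exploratory aims and gives it no time point. It also sets the calendar: "Adolescents will be involved in the trial for approximately 5 weeks with a 3-month follow-up assessment".

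The section on consultation with topical experts (Phases 5 to 6) describes how referral will work in the trial: "we will provide a daily update to StrongMinds counselors with a list of contact numbers of adolescents who screened positive".

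**The concern.** The abstract makes a dated commitment that the measurement schedule does not support. If the team follows Table 2, students are not asked about counseling sessions at the 3-month visit, and that self-report is hard to recover once the visits have passed.

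There is a second, softer issue. Referral runs through the intervention, so a student who screens positive near the end may have a first session only after the one post-baseline count. The linkage proportion would then partly reflect when the count was taken.

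The Limitations section says the preliminary data, including those on linkage to behavioral health care, will be the basis for a larger trial. A linkage figure without a stated window is a weak planning input.

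**Working it through.** The plan states no figure on this point to reproduce. The check is a comparison of sections, followed by one illustration.

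**Step 1. Is a 3-month evaluation of linkage intended?**
- Abstract, Methods: yes, explicitly.
- Statistical Analysis, first subsection: all metrics are to be compared between arms at baseline, at the post-intervention assessment and at the final 3-month assessment. This is general, but it points the same way.
- Procedures: linkage is exploratory, with no time given.

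**Step 2. Is the measurement scheduled at 3 months?**
- Table 2, counselor-session row: no.
- Measures, Overview: self-reported linkage will be confirmed with a StrongMinds counselor. No date is given. The step confirms a self-report, and none is scheduled at 3 months. The confirming source also differs from the school and clinic records named in Table 2.
- Behavioral Health Screeners via Mobile Phone: the same behavioral health measures are placed in the baseline and 3-month batteries. The heading and context concern the symptom screeners, and sessions are not named. The sentence also disagrees with Table 2, where PHQ-9, GAD-7 and AUDIT-C stop at the post-intervention assessment.
- Secondary End Point Analysis: behavioral health status and PrEP knowledge are reanalyzed at 3 months. Sessions are not named.

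**Step 3. Contrast with other rows.** HIV testing has all three time points, each with its own look-back period (past year, study period, past 3 months). Self-efficacy, which includes contacting a behavioral health counselor, is also collected at 3 months. As scheduled, the trial would record confidence in contacting a counselor at 3 months but not whether contact took place.

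**Step 4. Could the post-intervention count miss sessions?** The documents give neither the delay from positive screen to first session nor the spread of positive screens over time. Purely as an illustration, assume referrals spread evenly over 5 weeks (35 days), a fixed delay of L days, and an assessment d days after the intervention ends. The share of first sessions falling after the assessment is then max(0, L − d)/35.

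| L (assumed) | d = 0 (end of week 5) | d about 30 (one month later) |
|---|---|---|
| 7 days | 7/35 = 20% | 0% |
| 14 days | 14/35 = 40% | 0% |
| 21 days | 21/35 = 60% | 0% |

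The value of d is itself unclear. Table 2 says immediately after the intervention, while the Statistical Analysis section speaks of a 1-month postintervention assessment. On these assumptions the loss runs from nil to 60%, which shows only that the documents do not determine it.

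**The case against.** The strongest reply is that the Time column of Table 2 may simply be incomplete for the whole behavioral-health block. The screener section and the Secondary End Point Analysis both expect 3-month behavioral health data that Table 2 omits, and the analysis section compares all metrics at 3 months. Figure 2, the timeline of measures, is not shown and may schedule counselor sessions. This reply has force: the mismatch may be a table error rather than a decision to stop collecting. It does not remove the conflict, because Table 2 states a time for this row and that time disagrees with the abstract.

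Two stronger readings are tempting and are not supported.
- A reader might infer that the 3-month result will have no data at all. The undated confirmation with the counseling partner could yield later records, so what is missing is a scheduled collection.
- A reader might infer that students referred late are counted as not linked. No such rule is written. Only first sessions falling after the assessment could be missed, not late referrals as a class. The reference to a weekly topic in the Phases 5 to 6 section also gives no support for an even spread of positive screens.

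The outcome's standing limits the weight of the point. Procedures makes linkage exploratory, HIV testing is the primary outcome, and the pilot's stated main purpose is acceptability and feasibility.

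**Conclusion.** The inconsistency holds. The abstract promises a 3-month evaluation of linkage, and Table 2 schedules counselor sessions only at baseline and immediately after the intervention. No section shown clearly fills the gap. This conclusion rests on the text alone and needs no numerical assumption, though the Figure 2 timeline could not be checked.

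The possible undercount at the post-intervention assessment is a secondary remark. Its size depends on an unstated referral-to-session delay and on when that assessment takes place, and it may be nil. It should not be quoted as an expected bias.

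No primary analysis or power statement is affected. The point is worth correcting because the abstract names linkage as an efficacy target, the result is meant to inform a larger trial, and the correction is cheap.

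**What to change.** Add the 3-month follow-up to the counselor-session row of Table 2, using self-report plus the confirmation already planned. State the window each count covers, as the HIV-testing row already does. Then align the abstract, Table 2, the Measures overview, the screener section and the first Statistical Analysis subsection on three matters: when sessions are collected, which records confirm them, and when the post-intervention assessment takes place.

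If 3-month collection is not wanted, remove the 3-month linkage evaluation from the abstract and report linkage as of the post-intervention assessment only.

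The first option costs one survey item at an existing visit, one later check of confirmation records and edits to the text. The second costs wording only.
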